### Outcome measures

2.2

The primary outcome measure in REFINE is progression free survival (PFS). PFS is defined as the interval from randomisation to first evidence of local recurrence, new primary cancer, distant metastases (new or progression), or death from any cause, whichever occurs first. Analysis will be performed approximately 6 months after stage I recruitment has completed and will inform the design of the second stage.

The following secondary outcome measures will be analysed:

Overall survival (OS)Quality of Life (QoL) (EORTC QLQ-C30 and EQ-5D-5L)Treatment-related toxicityMean incremental cost per patientMean incremental QALYs per patient (calculated from EQ-5D-5L)Cost-utility analysis assessing cost-effectiveness of reduced versus standard frequency administrationFeasibility of recruitment to each cohort

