### Sample size

2.3

REFINE will enrol 160 patients into stage I for each cohort (80 patients randomised to each arm). This will provide 80% power at a 5% one-sided significance level to detect an absolute reduction of 20 percentage points in 9-month PFS. This number of patients would also be sufficient to demonstrate non-inferiority of the extended frequency arm, using a hazard ratio non-inferiority margin of 1.94 for the renal cohort (and e.g. 1.85 for the melanoma cohort) which should correspond to a 20-percentage points NI margin on the 9-month PFS difference scale. 9-month PFS rates are estimated to be 70% in the renal cohort [1,18]. For all cohorts, stage I analysis will be performed when approximately 30 PFS events have been observed in the control arm, which is expected to occur around six months after the completion of recruitment.

Following analysis of stage I data, assuming satisfactory outcomes in patients treated with the extended dosing interval, stage II will then test multiple experimental arms with the maximal interval being 3 times the SOC. The second stage intends to enrol up to an additional 200 patients per cohort dependent on stage I results. Under the same assumptions made for the stage 1 sample size calculations, this will provide around 80% power to demonstrate non-inferiority for the extended interval arm, relative to SOC using the same non-inferiority margins.

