### Health economic considerations

2.4

The economic evaluation for stage I of the trial will evaluate the relative cost-effectiveness of the two treatment frequencies over a 12-month period. The incremental cost per quality-adjusted life-year (QALY) gained will be calculated as recommended by the National Institute for Health and Care Excellence (NICE) [19], using QALYs calculated from EQ-5D-5L responses collected at baseline and every 12 weeks, including after progression [20], from the perspective of the NHS and Personal Social Services.

Resource use will be collected at baseline for the preceding 12 weeks and every 12 weeks thereafter from patient records and directly from participants via a modified version of the Client Service Receipt Inventory (CSRI) [21], covering inpatient and outpatient hospital service use, urgent care, primary and community health and social care service contacts, and therapies including ICI treatment costs, radiotherapy, surgery, and other systemic cancer treatments. Costs involved in administering ICI will be included in both arms.

Parameter uncertainty will be addressed using standard boot-strapping techniques and sensitivity analyses performed for any assumptions made. Further details will be described in the statistical and health economic analysis plan.

A lifetime decision analytic model will be constructed using information collected in stage I and stage II for those arms that are carried forward, to estimate the relative cost-effectiveness of the different treatment frequencies.

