### Participant follow up

2.12

Participants will be followed up for 1 year and 9 months from randomisation, regardless of treatment status or progression. Longer term data including information on progression and survival will be collected on an annual basis until the end of the trial.

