Analysis of PFS in stage II will be performed as described for stage I, fitting a Cox model for PFS and estimating hazard ratios comparing extended frequency arms to the standard frequency arm. A 5% (one-sided) significance level will be used throughout. Analysis will begin by assessing the most extended frequency arm. If that arm demonstrates non-inferiority, no further arms will be compared, and all arms will be considered for the phase III expansion of REFINE. If non-inferiority is not demonstrated, the next most extended frequency arm is assessed in the same manner, and so on until either an arm demonstrates non-inferiority, or all arms have been assessed.

If there is evidence of non-proportional hazards, or if other characteristics of the data suggest a likely gain in power, restricted mean survival (RMST) with a t-star of nine months will be used to analyse these data instead [24].

For time to event analyses, patients without an observed event will be censored at the date of their last assessment. It is anticipated that the majority of censoring will be administrative censoring at the time of analysis, therefore the assumption of non-informative censoring should be valid. Patterns of censoring will be assessed and if necessary, for example if a high proportion of patients are lost to follow-up, sensitivity analyses may be performed to assess the robustness of results.

Analysis of categorical variables will compare arms using the chi-squared or Mann-Whitney test, with analysis of continuous variables using a *t*-test. Continuous secondary outcome measures such as QOL may utilise linear mixed models to obtain an estimate for the mean difference between treatment arms. Models will include a random intercept, plus arm, time-by-arm interaction and randomisation stratification variables as fixed effects. Model assumptions will be examined using residual analysis and examination of graphical displays such as normal quantile plots. For quality-of-life analyses, initial analyses will use a complete case approach, without imputation of any missing data. Levels and patterns of missing data will be assessed, and if necessary, sensitivity analyses will be conducted using multiple imputation techniques.

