All estimates will be presented along with their 95% confidence interval. Additionally, to assess non-inferiority, PFS hazard ratios will also include a 90% confidence interval, corresponding to the 5% one-sided significance interval. All disease cohorts are designed to be independently powered and analysed.

All analyses will be conducted using the intention-to-treat (ITT) population, including all randomised patients. The primary outcome measure of PFS will also be assessed using the per-protocol (PP) population, which will exclude any ineligible patients, and any patients who do not receive any treatment after randomisation.

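### The quality-of-life mixed model names a random intercept as its only within-patient term alongside time-by-arm, so intervals for slope and late-visit contrasts may be too narrow (minor)

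*Protocol article*

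**What the plan says.** All references are to the protocol article; the full analysis plan is not shown.

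- Section 2.18 (Statistical analysis plan) makes the mixed model optional and states its purpose: "Continuous secondary outcome measures such as QOL may utilise linear mixed models to obtain an estimate for the mean difference between treatment arms".
- It then lists the terms: "Models will include a random intercept, plus arm, time-by-arm interaction and randomisation stratification variables as fixed effects". No random slope or residual covariance is named, and time is not said to be linear or categorical. No test of the interaction is announced.
- On checking: "Model assumptions will be examined using residual analysis and examination of graphical displays such as normal quantile plots". On reporting: "All estimates will be presented along with their 95% confidence interval".
- Section 2.4 (Health economic considerations) gives the schedule, for EQ-5D-5L only: "EQ-5D-5L responses collected at baseline and every 12 weeks, including after progression".
- Section 2.12 (Participant follow up): "Participants will be followed up for 1 year and 9 months from randomisation, regardless of treatment status or progression".
- Section 2.2 lists QoL (EORTC QLQ-C30 and EQ-5D-5L) as secondary. Under section 2.18, if stage I PFS shows neither inferiority nor non-inferiority, the committees weigh QoL and safety alongside efficacy. No QoL threshold is set.

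**The concern.** A mixed model with only a random intercept lets patients differ in level but not in direction. Scores 12 weeks apart and 84 weeks apart are assumed equally correlated, and every patient in an arm is assumed to change at the same rate. That is unlikely in this population. Follow-up runs through response, progression and changes of treatment, and sections 2.9 and 2.10 let extended-interval patients return to the standard interval after progression.

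If patients' slopes do vary, that variation belongs in the standard error of the time-by-arm term, because the patient is the unit randomised. The named model leaves most of it out. The resulting intervals could suggest a QoL gain or loss from the extended interval that the data do not support. QoL is part of the rationale for the trial and one input to the choice of stage II arms when PFS is inconclusive. The issue is separate from which fixed effects are listed: it remains if a time main effect is added.

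**Working it through.** The article gives no QoL standard deviation, correlation or power, so there is no stated figure to reproduce.

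**Inputs from the article**
- 80 patients per arm (section 2.3).
- Visits every 12 weeks, h = 12/52 = 0.2308 years (section 2.4).
- 21 months of follow-up is about 91 weeks: visits at weeks 0 to 84, K = 8. A 12-month window gives weeks 0 to 48, K = 5.
- 95% intervals, that is, two-sided 5%.
- Stage I analysis about 6 months after roughly 12 months of recruitment (section 2.15). Follow-up is then about 26 to 78 weeks, or 3 to 7 visits.

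**Assumptions, not from the article**
- A 0-100 scale, intercept SD 15, residual SD σ = 13 (σ² = 169), linear time.
- Patient slope SD τ = 5, 10 or 15 points per year, or serial correlation of 0.8 to 0.9 per visit.

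**Slope term, balanced visits**
- Sxx = h²·K(K²−1)/12. For K = 8: 0.05325 × 42 = 2.237. For K = 5: 0.05325 × 10 = 0.5325.
- True variance of a patient's fitted slope: τ² + σ²/Sxx.
- Variance that the random-intercept model attributes to it: τ²/(K−1) + σ²/Sxx, because slope variation is pooled into the residual.
- R = true/attributed. Actual size of the test = 2·[1 − Φ(1.96/√R)].
- σ²/Sxx is 75.56 for K = 8 and 317.3 for K = 5.

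| K | τ | True | Attributed | √R | Size |
|---|---|---|---|---|---|
| 8 | 5 | 100.6 | 79.1 | 1.127 | 8.2% |
| 8 | 10 | 175.6 | 89.8 | 1.398 | 16.1% |
| 8 | 15 | 300.6 | 107.7 | 1.671 | 24.1% |
| 5 | 5 | 342.3 | 323.6 | 1.029 | 5.7% |
| 5 | 10 | 417.3 | 342.3 | 1.104 | 7.6% |
| 5 | 15 | 542.3 | 373.6 | 1.205 | 10.4% |

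With τ = 0, R = 1 and the size is 5.0%. √R is also the factor by which the interval should be wider.

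**Stage I follow-up.** With uniform entry and 3 to 7 visits, the slope-term sizes are 6.4%, 10.5% and about 16% for τ = 5, 10 and 15. With serial correlation of 0.9 and 0.8 per visit plus measurement error they are 9.8% and 11.3%.

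**Serial correlation, 8 visits.** A simulation with 0.9 and 0.8 per visit plus measurement error gave 17.8% and 19.6%. Its split of the variance may differ from the stage I check, so the two sets are not strictly comparable. Pure serial correlation without measurement error, 0.5 to 0.9 per visit, is more extreme: 18.0-31.6% with 8 visits.

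**Other contrasts under the same model**
- Difference at the last visit, linear time: 6.7%, 11.0% and 15.6% with 8 visits; 5.5%, 7.0% and 9.1% with 5.
- Categorical time, over all covariances tried: omnibus interaction 5.0-10.3%, change from baseline to last visit 5.0-16.7%, last-visit difference 5.0-12.4%.
- Arm difference averaged over visits: 5.0% in every balanced scenario and 5.0-5.3% under stage I follow-up.

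**Simulation check.** REML fits of the random-intercept model used 1,500 trials per scenario, with 0% or 8% dropout per visit. The slope term at τ = 15 ran at 9.4-10.9% with 5 visits and 23-24% with 8. The arm mean difference ran at 4.4-6.2%, where the Monte Carlo standard error is √(0.05 × 0.95/1500) = 0.56 points. In separate fits at τ = 10 with 8 visits, the slope-term size was 16.3% or 16.0% depending on whether a time main effect was included. Allowing patient-specific slopes brought the test to 4.5-5.8% in every scenario.

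**The case against.** The strongest reply is that the article does not announce the test that goes wrong. Its stated purpose is a mean difference between arms, and averaged over visits that difference keeps its level. This stands, and it limits the point. It does not remove it: once time-by-arm is in the model, no single coefficient is the visit average (with linear time, the arm coefficient is the difference at time zero). The article does not say which contrast will be reported, and it promises a 95% interval for all estimates.

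Second, the model is optional, assumptions will be examined, and a condensed article may leave the residual covariance to the full plan. This also stands. A random intercept can be combined with a serial or unstructured residual covariance, so independent residuals are one reading and not a stated choice. But the article does list the model's terms, and the checks it names come with no alternative covariance.

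Three stronger readings are tempting and not supported:

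- A reader might infer that the plan commits to a QoL test with an error rate of up to 24%. No interaction test is declared, and that figure needs a slope SD of 15 and all 8 visits. No patient can have 8 visits at the stage I analysis on the stated timeline.
- A reader might infer that repeated scores are treated as independent. They are independent only given the patient intercept; constant within-patient correlation is modelled.
- A reader might infer that a false QoL result would decide stage II. QoL is one of several inputs to committee judgement, without strict rules.

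**Conclusion.** The point holds in conditional form and is minor. If the random intercept is the only within-patient term, residuals are otherwise independent, and patients' slopes differ or correlation decays, then intervals for the time-by-arm term and late-visit differences are too narrow. Under the assumed variances and linear time, a nominal 5% test of the slope term runs at about 6-16% with stage I follow-up and about 8-24% with 8 visits. Nominal 95% intervals would then cover about 84-94% and 76-92%. Over all covariances tried the range is about 5-32%, and the excess vanishes if slopes are equal and correlation is constant. The article supplies none of these variances, so the sizes illustrate the problem and do not estimate it. The 12-weekly schedule is stated for EQ-5D-5L only; applying it to QLQ-C30 is a further assumption. The visit-averaged arm difference and the primary Cox analysis of PFS are not affected.

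**What to change.** In the analysis plan:

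1. Name the QoL treatment contrast, for example the arm difference averaged over visits or the difference at a stated visit.
2. Replace the random intercept as sole within-patient term with one of: categorical visit with unstructured within-patient covariance and a small-sample degrees-of-freedom correction (preferred); a random intercept and random slope for time with unstructured covariance; or robust standard errors clustered on patient.
3. State a fallback covariance structure in case the model does not converge.

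This takes a few sentences and no new data. The cost is wider intervals for slope and time-specific contrasts: under the assumptions above, the slope interval would be about 1.13 to 1.67 times as wide with 8 visits. If the full plan already specifies these items, nothing further is needed.

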### Statistical analysis plan

2.18

For stage I, the primary analysis will consist of a Cox proportional hazards model, where time will be time to progression or censoring, and the main covariate will be binary treatment, defined as standard-of-care (Arm A – standard frequency) or extended frequency (Arm B) ICI. The model will also adjust for the stratification variables. Each cohort will be analysed separately, using a 5% one-sided significance level. All patients will be included and analysed by their schedule allocation (intention to treat – ITT). The hazard ratio for Arm B vs Arm A will then be estimated and will inform the design of stage II, following discussion with relevant oversight committees (Trial Management Group (TMG), Independent Data Monitoring Committee (IDMC) and Trial Steering Committee (TSC)). Strict statistical rules will not be in place, but decisions will be based on the following guidelines:

If the stage I analysis shows that the extended interval arm (2×) is significantly inferior to the standard interval arm (1×), i.e. the confidence interval (CI) for the hazard ratio lies entirely above 1, recruitment will not be continued in the 2× arm, and no arms with further extended intervals (2.5× or 3×) will be opened. The trial committees will discuss whether there is any scientific merit in opening the intermediate interval (1.5×) arm (Fig. 1).If the extended frequency arm is not shown to be significantly inferior, an assessment of non-inferiority will be made. If non-inferiority is shown, (CI for the hazard ratio excludes the non-inferiority margin), then stage II can proceed as planned, opening up arms with further extended intervals (2.5× and 3×). The trial committees will further discuss whether there is merit in adding the intermediate interval (1.5×) arm at this stage.In the event that the stage I results show neither inferiority or noninferiority of the extended frequency arm, (CI for the hazard ratio includes both 1 and the non-inferiority margin), the trial committees will determine which arms will be available in stage II. Safety and quality of life data will be considered alongside the efficacy data, as well as any emerging external evidence, including information from other REFINE cohorts.

Decisions will be made independently for each cohort; not all cohorts may continue to stage II, and different arms may be introduced in each cohort.

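### The quality-of-life mixed model lists a time-by-arm interaction without a time main effect; under 0/1 product coding, a change common to both arms is credited to the extended-interval arm

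*Protocol article*

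**What the plan says.** Section 2.2 of the protocol article (Outcome measures) names quality of life as a secondary outcome: "Quality of Life (QoL) (EORTC QLQ-C30 and EQ-5D-5L". Section 2.18 (Statistical analysis plan) says how it may be analysed: "Continuous secondary outcome measures such as QOL may utilise linear mixed models to obtain an estimate for the mean difference between treatment arms". The next sentence fixes the terms: "Models will include a random intercept, plus arm, time-by-arm interaction and randomisation stratification variables as fixed effects". Neither time nor the baseline score is in that list. The section does not say whether time is continuous or categorical, how the interaction is coded, or whether the baseline score is one of the repeated responses.

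Section 2.4 (Health economic considerations) shows that a baseline score exists for one of the two instruments: "EQ-5D-5L responses collected at baseline and every 12 weeks, including after progression". On missing data, section 2.18 says that "initial analyses will use a complete case approach, without imputation of any missing data", with multiple imputation as a sensitivity analysis if needed.

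The results have a limited role in decisions. If stage I shows neither inferiority nor non-inferiority, "Safety and quality of life data will be considered alongside the efficacy data" when the committees choose stage II arms.

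**The concern.** An interaction without its time main effect is a restricted model. With arm coded 0 for standard interval and 1 for extended interval, and a single arm × time product, the fitted means are:

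- standard interval: b0 (constant over time)
- extended interval: b0 + b1 + b2 × time

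The standard arm has no slope. If scores drift in both arms, as they may in advanced cancer, the model can express that drift only through b2. The drift is then read as an effect of the dosing interval, and b1 moves the other way to compensate.

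A better quality of life is one of the claimed benefits of extended dosing, and these data may be weighed when stage I is inconclusive. A false difference, or a real one masked by a common trend, could therefore enter the stage II discussion.

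**Working it through.** The plan gives no figure for quality of life, so there is none to reproduce. The check is of the model itself.

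**Inputs from the protocol article.** 80 patients per arm (section 2.3: "REFINE will enrol 160 patients into stage I for each cohort (80 patients randomised to each arm"); assessments at baseline and every 12 weeks (stated for EQ-5D-5L, section 2.4); the terms listed in section 2.18.

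**Assumptions, not in the article.** SD 20; within-patient correlation r of 0.5 or 0.6; a common linear trend d per 12 weeks; no true arm effect; two-sided 5% test; no missing data unless stated.

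**1. Expected estimates under 0/1 product coding, balanced data.** Count time in 12-week units.

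- The standard arm is fitted by its average, d × (mean time). The extended arm is fitted by its true line.
- So b2 = d, and the fitted arm difference at time t is d × (t - mean time).
- With visits at 0, 12, 24, 36 and 48 weeks (t = 0 to 4, mean 2) and d = -1: b2 = -1.0, b1 = +2.0, and the difference at week 48 is -1 × (4 - 2) = -2.0. All three should be 0.
- The difference averaged over the visits is +2.0 - 1.0 × 2 = 0, which is correct.

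**2. False significance of the interaction.** SE(b2) = √[SD² × (1 - r) / (n × Sxx)], where Sxx is the sum of squared deviations of the visit times. The rejection rate is Φ(z - 1.96) + Φ(-z - 1.96), with z = |d| / SE.

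| Visits | r | d | SE | z | Rejection |
|---|---|---|---|---|---|
| 5 (Sxx = 10) | 0.5 | -1 | √(200/800) = 0.50 | 2.00 | 52% |
| 4 (Sxx = 5) | 0.6 | -1.5 | √(160/400) = 0.63 | 2.37 | 66% |
| 5 (Sxx = 10) | 0.5 | -2 | 0.50 | 4.00 | 98% |

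Simulation agrees. With five visits and 2,000 runs, the rates are 5.6%, 52.7%, 97.9% and 100% for trends of 0, -1, -2 and -3. The four-visit case gave 63% in 150 fits.

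**3. With time added.** The expected interaction is 0 for any common trend, and the simulated rejection rate is 4.5% to 6.0% in the same five-visit runs.

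**4. Dropout.** Take five visits, r = 0.5, d = -2 and 10% dropout per visit, equal in both arms. The standard arm's constant is now pulled towards the better-observed early visits and is fitted at -3.28. The extended arm averages -2 × 2 = -4.00. The visit-averaged difference is -4.00 + 3.28 = -0.72, with an SE of about 2.6. With time included it is 0.

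**5. Other coding.** If the interaction is entered as one time term per arm, the model spans the same space as arm × time with both main effects: 4 columns against 4 with linear time, 10 against 10 with categorical time. There is then no bias.

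**6. Baseline covariate.** If only follow-up scores are modelled, with four visits and equal correlation r throughout, adding the baseline score multiplies the variance of the mean difference by 1 - r² / [r + (1 - r)/4].

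- r = 0.4: 0.16/0.55, a cut of 29%
- r = 0.5: 0.25/0.625, a cut of 40%
- r = 0.6: 0.36/0.70, a cut of 51% (SE from √(10 × 0.70) = 2.65 to √(10 × 0.34) = 1.84, where 10 = 2 × 400/80)
- r = 0.7: 0.49/0.775, a cut of 63%

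**The case against.** The strongest reply is that the article does not state the coding. A statistician who fits arm plus arm-specific time terms has the correct model, and many would do so without thinking of it as a departure. This stands, and it makes the bias conditional. It does not remove the point, because the result should not depend on how a program expands the interaction.

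Four stronger readings are tempting, but the article does not support them.

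- **That the reported treatment effect is biased.** The stated target is the mean difference between arms. Averaged over visits, this is unbiased with balanced data even under the literal model (simulated rejection 4.8% to 6.3%), and the dropout bias in the example is small against its SE. The high false-positive rates concern the interaction. The article does not say which contrast will be reported.
- **That precision is certainly lost.** The gain in step 6 requires a follow-up-only model. If the baseline score is already a repeated response, the random intercept uses it. The change-from-baseline contrast then has 1.84, 1.00 or 0.48 times the variance of the follow-up-only contrast at correlations 0.3, 0.5 and 0.7. Handling of baseline is also commonly left to the full protocol or analysis plan, which are not shown.
- **That partly observed patients will be dropped.** The complete-case phrase goes on to say that nothing is imputed, which fits using every observed assessment. Section 2.18 also says that all analyses include all randomised patients.
- **That a random intercept alone is wrong.** An unstructured covariance or a random slope is a reasonable preference, not a correction.

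The size also depends on the assumed trend: with no common trend, the false-positive rate is nominal.

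**Conclusion.** The point holds in a limited form. Section 2.18 lists specific fixed effects and leaves out time. Followed literally, with a 0/1 product term, the model attributes any common trend to arm in the interaction, the arm coefficient and visit-specific differences. That direction needs no assumption beyond the coding and a nonzero trend. The size, about 52% to 98% false significance of the interaction against about 5% with time included, rests on the assumed SD, correlation and trend.

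Severity is minor. The model is optional, the outcome is secondary, and quality of life is named as supporting information for stage II only when stage I is inconclusive. The PFS analysis, the sample size and the non-inferiority margin are unaffected, and no stated figure is shown to be wrong.

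**What to change.** Amend the sentence in section 2.18 so that the fixed effects read: time (visit), arm, time-by-arm interaction, baseline score and the stratification variables. State that the responses are the follow-up scores, so that the baseline score is used once, as a covariate. Section 2.4 shows that it is collected for EQ-5D-5L.

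It would also help to name the contrast that will be reported as the mean difference.

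The cost is a sentence or two of wording before the stage I data are analysed, with no new data and no change to the sample size.
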